## Abstract

**Background:**

A significant proportion of the overall cost of total hip arthroplasty (THA) results from the inpatient hospital stay following the procedure. Considering the substantial and increasing number of these procedures performed annually, shifting to an outpatient model of care where the patient is discharged home the same day as their surgery represents a potential for significant cost savings. The potential significant impact of an outpatient care model on constrained healthcare budgets and lack of high-quality evidence regarding its effectiveness warrants a rigorous comparative trial. The purpose of this prospective, randomized controlled trial is to evaluate outpatient care pathways for THA. Specifically, our objectives are to compare the rate of serious adverse events and estimate the cost-effectiveness of outpatient compared to standard inpatient THA.

**Methods:**

We will include patients undergoing primary THA whom have an American Society of Anaesthetists status equal to or less than three, live within a 60-min driving distance of the institution and have an adult to accompany them home postoperatively and stay with them overnight. Consenting patients will be randomized to be discharged on the same day as surgery, as outpatients, or as inpatients according to standard of care (minimum of one night in hospital) using a modified Zelen consent model. The primary outcome measure is the incidence of serious adverse events at 30 days postoperative. Participants and their caregivers will complete secondary outcomes measures at each follow-up visit including patient-reported outcome measures and self-reported cost questionnaires.

**Discussion:**

This protocol is the first randomized trial to use blinding to evaluate outpatient THA compared to standard overnight stay and first to prospectively perform a full economic evaluation. It is also the first adequately powered trial to prospectively assess the safety of outpatient THA. Successful completion of this study could have the potential to provide clinical evidence for the role of outpatient THA in current practice.

**Trial registration:**

This study was retrospectively registered on ClinicalTrials.gov (NCT03026764) on March 9th, 2016.

## Background

Osteoarthritis (OA) is a leading cause of disability and reduced quality of life, presenting a substantial, growing burden to patients and the healthcare system [1]. Total hip arthroplasty (THA) is an established, effective intervention for advanced OA. The prevalence of hip OA is rapidly increasing, resulting in a rising demand for care. The number of THA procedures is projected to grow by 71% between 2014 and 2030 in the US [2]. Currently, THA, along with total knee arthroplasty (TKA), have a significant impact on healthcare budgets, costing approximately $1.2 billion in annual spending in Canada [3]. These staggering numbers highlight the critical need to improve care delivery.

A significant proportion of the overall cost of joint replacement results from the inpatient hospital stay following the procedure. Historically, the standard procedure following THA required an inpatient hospital stay of two and a half to 3 weeks, however the introduction of less invasive surgical techniques, improved medical and analgesia management and comprehensive rehabilitation have enabled shorter inpatient stays. Today, the median inpatient stay following THA is 3 days in Canada [3]. A desire for greater autonomy by the patients as well as patients wanting early mobilization to accelerate recovery and return to activities has led some clinicians to consider an outpatient arthroplasty program. The proposed benefits of outpatient arthroplasty include similar patient outcomes with significantly lower hospital costs, and improved patient satisfaction, independence, and autonomy. However, there is a lack of high-quality evidence comparing clinical outcomes of outpatient to inpatient arthroplasty models of care.

A retrospective analysis of over 50,000 THA and TKA procedures found no differences in 30-day major complications or readmissions among patients with a zero to two-day hospital stay compared to those discharged on day three or four postoperative [4]. Small cohort studies [5–8] suggest lower costs for outpatients and improved patient satisfaction but have inherent biases as they are limited to carefully selected patients in privatized health systems.

It is estimated that up to 20% of the overall cost of THA can be attributed to the inpatient stay in hospital at our institution [9]. By discharging patients as outpatients, it could be possible to have substantial savings. Although these preliminary calculations are encouraging, it is not sufficient to effect change solely to achieve cost control, without consideration of safety, effectiveness and patient satisfaction. Further, it is unknown whether the financial savings will be outweighed by additional postoperative costs, increased readmissions or decreased quality of care. A full economic evaluation that simultaneously evaluates cost and effectiveness is crucial prior to implementation. The lack of high-quality evidence regarding its effectiveness warrants a rigorous comparative trial.

The purpose of this study is to evaluate outpatient care pathways for THA. Specifically, our objectives are to compare the rate of serious adverse events and estimate the cost-effectiveness of outpatient compared to standard inpatient THA using a patient-blinded, randomized clinical trial.

## Methods/design

### Study setting

Patients will be recruited from two orthopaedic centers in Canada (London Health Science’s University Hospital, London ON and St. Michael’s Hospital, Toronto ON). The surgeons will screen potential participants in their clinics and provide an overview of the research study (Fig. 1).

**Fig. 1 Fig1:**
[figure not shown]
Participant flow through the study

### Eligibility criteria

We will include patients undergoing primary THA. Eligible patients will have an American Society of Anesthetists (ASA) status equivalent or less than three, the ability to read and understand English, live within a 60 min commute distance of the institution, have access to a phone, and sufficient caregiver support. We will exclude patients with a history of anesthesia related complications, narcotic dependency, anaphylaxis to penicillin, significant psychosocial issues that influence safety, or cognitive issues that preclude the ability to understand instructions. We will also exclude patients whom have fibromyalgia, are skeletally immature, have an active or suspected latent infection in or about the joint, bone stock inadequate for support or fixation of the prosthesis, are unable to go to their home after surgery, have neuromotor conditions, significant pain management issues or obesity that significantly impacts their ability to mobilize (Table 1).

**Table 1 Tab1:** Eligibility Criteria

Inclusion Criteria	Exclusion Criteria
1. Primary THA	1. Fibromyalgia
2. ASA status ≤3	2. Skeletally immature
3. Ability to read and understand English	3. Cognitive or neuromotor conditions
4. Live within 60-min commute distance of hospital	4. Bone stock inadequate for support or fixation of prosthesis
5. Home/cell phone access	5. Unable to go to their home after surgery
6. An adult to accompany patient home postoperatively	6. Active or suspected latent infection in or about the joint
	7. Significant pain management issues
	8. Patient/family history of anesthesia related complication(s)
	9. Obesity that significantly impacts the patient’s ability to mobilize
	10. Anaphylaxis to penicillin
	11. Significant psycho/social issues that would prevent the patient from managing at home safely
	12. Narcotic dependency

### Interventions

All patients will undergo a primary unilateral THA. All THA procedures will be performed using a direct anterior surgical approach according to the surgeon’s standard of care. The specific surgical pathway details (anesthetic, implants, etc.) will not be standardized for this study to maintain generalizability.

Both inpatient and outpatient care models begin with comprehensive preoperative patient education to equip the patient with a reasonable set of goals and expectations about their surgery, medications, pain management and rehabilitation. Immediately following surgery, the primary goals are to treat pain, nausea and hypovolemia. The combination of this early rehabilitation program, with a muscle sparing technique, is vital to the rapid recovery process. The surgical technique minimizes blood loss, provides a stable construct to facilitate immediate weightbearing, minimizes soft tissue trauma and includes a peri-articular injection. Home-based physical therapy should begin immediately, with a focus on ambulation.

Perioperative care and discharge protocols will be similar for both care models. Standard discharge criteria includes: ability to use required gait aids, appropriate pain control, control or absence of nausea and vomiting, hemostasis at the surgical wound, hemodynamically stable with appropriate laboratory values, alert and oriented, able to use the bathroom, meets the hospital standard targets from physiotherapy for discharge, given take-home medications, and in the company of a caregiver. Potential complications are also discussed so the patient understands the normal course of recovery as well as signs or symptoms that may be cause for concern and additional consultation.

#### Patients randomized to inpatient

Patients allocated to the inpatient group will be discharged home according to standard protocol at each site (typically one to 4 days postoperative).

#### Patients randomized to outpatient

Patients allocated to the outpatient group will be discharged home on the same day as the procedure. These patients will receive an additional physiotherapy session prior to surgery where they are instructed to practice certain skills such as bed transfer, cane/crutches use and gait training.

### Outcomes

We will collect outcome data preoperatively and at follow-up visits at discharge, 2 weeks, 6 weeks and 3 months postoperative, which is in keeping with usual practice patterns. We will record anaesthesia and surgical time and blood loss for each procedure and demographic information including date of birth, sex, height, weight, smoking status, and comorbidities.

#### Primary outcome

Given that the primary concern with sending patients home earlier than usual is an increase in the number or severity of early post-operative complications, our primary outcome is any serious adverse event within the first 30 days postoperative. A serious adverse event is defined as any untoward medical occurrence that results in death, is life-threatening, requires inpatient hospitalization or causes prolongation of existing hospitalization, results in persistent or significant disability or incapacity, or requires intervention to prevent permanent impairment or damage [10–12].

#### Secondary outcomes

Our secondary outcomes include patient-reported satisfaction, health-related quality of life (HRQOL), function, pain, and caregiver assistance. Patients will be asked to rate satisfaction with pain control, safety and quality of care on either a 100-mm visual analogue scale (VAS) with a score of 100 representing the highest possible satisfaction, or on a five to seven-point ordinal scale (completely satisfied to completely unsatisfied).

We will measure HRQOL using the *Western Ontario and McMaster Universities Osteoarthritis Index* (WOMAC), which includes three arthritis-specific domains of pain, stiffness and physical function. It has demonstrated content, cross-sectional and construct validity, good internal consistency reliability and moderate to high test retest reliability in patients undergoing THA and TKA [13]. To measure function, we will use the *Harris Hip Score* (HHS) [14]; a valid and reliable objective functional measure completed by the surgeon. We will measure general health using the *12-Item Short Form Health Survey* (SF-12v2) and th*e European Quality of Life Scale* (EQ-5D). The SF-12 evaluates limitations on physical and social activities, activities of daily living, pain, mental health and well-being, and perceptions of health and is valid, reliable, and responsive in patients with arthritis [15]. The EQ-5D index includes domains of mobility, self-care, usual activities, pain, anxiety and depression and has good test retest reliability and cross-sectional construct validity in patients with arthritis [16]. We will measure pain using a self-administered *Numeric Pain Rating Scale* (Pain NRS), ranging from 0 (no pain) to 10 (worst). We will measure the level of assistance provided by the caregiver throughout the recovery period using the *Caregiver Assistance Scale* (CAS) [17] and *Caregiver Strain Index* (CSI) [18].

#### Cost

We will ask patients to report any calls to the surgeon’s office, the on-call resident, the orthopaedic outpatient clinic, emergency room visits or hospitalizations for the first 2 weeks postoperative. Patients will also complete a healthcare resource use diary at each follow-up. The diary includes information on emergency room visits, hospitalizations, family doctor, specialist, healthcare professional or outpatient clinic visits, tests, procedures, and prescription or over-the-counter medications and any other miscellaneous costs related to their joint replacement. We will also record employment status and time-off paid employment, homemaking or volunteer activities, for both patients and caregivers.

We will obtain surgical procedure costs from our institutions’ case costing department. The unit costs for additional resource use following surgery can be found in provincial fee schedules and drug benefit formularies. The average Canadian wage reported by Statistics Canada will be applied to place a monetary figure on time off paid employment, for both patients and their caregivers and the current value of minimum wage in the province of Ontario to account for lost time for those who were retired, as well as time away from volunteer or home making activities.

The total cost will be determined by multiplying the quantity of resource use by the corresponding unit cost, summing the total cost over each follow up interval, and then calculating the mean cost at each follow-up time point, as well as an overall mean cost for the entire study period.

### Participant timeline

Patients will be screened and consent obtained at the time of booking for surgery and baseline assessments will occur at the preoperative visit within 3 months of surgery. On the day of discharge from hospital, we will obtain a pain score from participants and provide them with a daily diary to record costs for the first 2 weeks. Postoperatively, participants will be seen at 2 weeks, 6 weeks and 3 months for follow-up.

We will ask caregivers to complete questionnaires preoperatively and at 2 weeks postoperatively (Table 2).

**Table 2 Tab2:** Participant Timeline

Assessments	Appointment				
	Baseline	Discharge	2 weeks	6 weeks	3 months
Demographics	X	–	–	–	–
Charlson Comorbidity Index	X	–	–	–	–
Self-Efficacy	X	–	–	–	–
Pain Catastrophizing Scale	X	–	–	–	–
Expectation Questionnaire: Preop	X	–	–	–	–
Surgical Information Form	–	X	–	–	–
Patient Flow	–	X	–	–	–
Pain NRS	X	X	X	X	X
SF-12v2	X	–	X	X	X
EQ-5D-5L	X	–	–	X	X
WOMAC	X	–	–	–	X
HHS	X	–	–	–	X
Adverse Event Form	–	X	X	X	X
Patient Satisfaction	–	–	X	–	–
Daily Diary	–	–	X	–	–
Patient Satisfaction and Expectations	–	–	X	X	X
Cost Questionnaire	–	–	X	X	X
Caregiver Demographics	X	–	–	–	–
Caregiver Assistance Scale	X	–	X	–	–
Caregiver Strain Index	X	–	X	–	–

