### Plan for statistical analysis

We will present the incidence of serious adverse events by group at 30 days postoperative and calculate a risk difference and relative risk with 95% confidence intervals around the estimates. The mean and standard deviation for all continuous outcomes (Satisfaction, WOMAC, SF-12, HHS, Pain NRS, and CAS) will be calculated for each group at each time point and calculate the mean between-group difference with 95% confidence interval. Linear mixed models, using a covariance structure that allows for correlations between measurements to decline as they are further apart in time will be used to evaluate improvements in function after surgery since this provides a powerful approach to analyze complex longitudinal data while controlling for important covariates such as gender, comorbidities, age and surgeon/site. All data will be analyzed according to the intention-to-treat principle with an as treated analysis also performed.

We will conduct a cost-effectiveness analysis from both a Canadian healthcare payer and societal perspective using the incidence of adverse events as our effectiveness outcome to estimate cost-effectiveness at 3 months postoperative. We will determine cost-effectiveness using the net benefit regression (NBR) framework to estimate the incremental net benefit (INB) of outpatient arthroplasty [22]. An intervention is considered to be cost-effective if the INB is greater than zero. NBR also provides a means to adjust for potentially confounding factors and therefore allows greater statistical efficiency and a more precise estimate of the INB. To characterize the statistical uncertainty around our estimate of INB we will calculate 95% confidence intervals, and a cost-effectiveness acceptability curve [23].

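### Adverse-event form and diary both start at discharge, so the first postoperative days are covered differently by arm; this may bias the adverse-event effect in the cost-effectiveness analysis

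*Protocol article*

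**What the plan says.** Under Outcomes, data are collected preoperatively and "at follow-up visits at discharge, 2 weeks, 6 weeks and 3 months postoperative". In the Participant timeline, the row "Adverse Event Form" of Table 2 is marked at those same four postoperative points and at no fixed early postoperative day. The text of that section adds: "On the day of discharge from hospital, we will obtain a pain score from participants and provide them with a daily diary to record costs". The diary covers two weeks.

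The time of discharge depends on the arm. For one arm: "Patients allocated to the outpatient group will be discharged home on the same day as the procedure". Patients in the other are "discharged home according to standard protocol at each site (typically one to 4 days postoperative").

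The Cost section asks patients to report calls to the surgeon's office, the on-call resident or the clinic, and "emergency room visits or hospitalizations for the first 2 weeks postoperative".

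The Plan for statistical analysis describes the economic evaluation as "using the incidence of adverse events as our effectiveness outcome to estimate cost-effectiveness at 3 months postoperative". The primary outcome is separate: any serious adverse event within 30 days of surgery.

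**The concern.** The first adverse-event assessment is tied to an event whose timing is the intervention itself. For an inpatient, the first one to four days lie before the discharge form. For an outpatient, everything after the first hours is first asked about on the two-week form. If minor events are recorded more fully close to when they happen, recorded incidence can differ between arms when true incidence does not.

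At stake is the effect side of the net benefit regression. Fewer recorded outpatient events would raise the incremental net benefit of outpatient care. The Blinding section expects no added detection bias because outcomes are patient-reported. That answers a question about who collects the data, not about when each arm is asked, and blinding of patients does not equalise the timing.

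**Working it through.** **1. Coverage of the early days, side by side** (Table 2 and the two arm descriptions; the two-week visit taken as day 14)

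| | Outpatient | Inpatient |
|---|---|---|
| Discharge, first form, diary handed out | day 0 | typically day 1 to 4 |
| Form that covers a day-1 event | two-week form | discharge form |
| Delay from a day-1 event to that form | 14 − 1 = 13 days | 0 to 3 days |
| Delay for a day-2 event, inpatient discharged on day 1 | 14 − 2 = 12 days | 14 − 2 = 12 days |

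The asymmetry is real, but for each inpatient it ends at that patient's discharge. It does not run to day 4 for everyone.

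**2. What else covers those days.** The contact reports in the Cost section are counted from surgery and apply to both arms. They pick up events that led to a call, emergency visit or admission. The diary's stated purpose is to "provide them with a daily diary to record costs for the first 2 weeks". It is not described as an event record, and outpatients receive it earlier. What remains is non-serious events without contact.

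**3. Which analysis is exposed.** With equal true incidence in both arms, let
- p = true proportion with at least one adverse event by 3 months;
- f = share of affected outpatients whose only event falls in the days covered by different forms;
- m = extra share of those events left unrecorded in the outpatient arm.

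Spurious risk difference favouring outpatient care: d = p × f × m. Incremental net benefit is λ × (events avoided) − (added cost), with λ the value placed on avoiding an event, so the artefact adds λ × d. The article gives no λ.

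**4. Size.** The article gives none of p, f or m. All of the following are assumptions:
- low: 0.20 × 0.20 × 0.10 = 0.004, or 0.4 points;
- middle: 0.40 × 0.40 × 0.25 = 0.04, or 4 points;
- high: 0.60 × 0.60 × 0.50 = 0.18, or 18 points.

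**5. Scale.** The plan has no figure on this point. Its sample size reproduces at 8% risk in both arms, a 6-point margin, one-sided 5% and 80% power: (1.645 + 0.842)² × 2 × 0.08 × 0.92 / 0.06² = 252.9, so 253 per arm and 506 in total. With 253 per arm, recorded incidences of 40% and 36% have a standard error of √(0.40 × 0.60/253 + 0.36 × 0.64/253) = 0.043. The middle case is thus about 0.04/0.043 = 0.9 standard errors.

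**The case against.** The best case against the point is that the mechanism is not on the page. The article does not say who completes the adverse-event form or from which source, and a full protocol may. A reader might infer that ward staff chart inpatients' events while outpatients' events rest on recall alone. Neither is stated. The discharge criteria, such as control of nausea and vomiting and hemostasis at the wound, show that such matters are assessed before discharge, not that they are entered as trial events. The contact reports also mean that outpatients' early days are not left to recall alone.

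The direction can also be disputed. Outpatients hold the diary from day 0, which may prompt fuller reporting. The Blinding section itself posits that some outpatients may be more likely to return for care, which would raise their recorded events. A bias towards outpatient care is therefore the likely direction for minor events, not a certain one.

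Finally, the stated objectives name serious events only, so the adverse-event wording in the economic analysis could be shorthand. If it is, little of the point remains.

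These arguments limit the point without removing it. The schedule is stated, it differs by arm, and nothing in the article gives both arms a common early assessment.

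**Conclusion.** The point holds in a limited form. The first postoperative days are covered by different forms at different times in the two arms. Non-serious events without contact may be recorded less completely for outpatients. This would probably favour outpatient care in the cost-effectiveness analysis, provided that the effect measure means all adverse events, as worded.

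The size cannot be computed from the document. The 0.4 to 18 points are a range over assumed inputs, not an estimate. Crediting every inpatient with in-hospital capture through day 4 would overstate it, since many may leave earlier. Patients with another recorded event count in any case, which also shrinks it.

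A reader might infer that the primary non-inferiority comparison is compromised. The document does not support that. Serious events are defined by death, threat to life, hospitalisation or its prolongation, lasting disability, or needed intervention, and are much less open to recall loss within 30 days. The hospitalisation parts of the definition could also pull in opposite directions: inpatients have more stay to prolong, while an unplanned admission of an outpatient may count.

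**What to change.** Recruitment is described as ongoing, so the change can still be made.

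- Hand out the diary on the day of surgery in both arms.
- Add a short adverse-event checklist for the same fixed postoperative days in both arms, for example days 0 to 14, filled in wherever the patient is.
- Ascertain events on those days from the same sources in both arms.
- State whether the effect in the net benefit regression counts all adverse events or only serious ones.
- Keep all recorded events in the main cost-effectiveness analysis. Add a sensitivity analysis limited to events captured by the common route plus serious events from any source. Making that restriction the main analysis would discard genuine non-serious events recorded in hospital, so it should stay a sensitivity analysis.

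The cost is a revised diary page, an earlier hand-out, slightly more patient burden, and a sensitivity analysis for patients enrolled before the change.
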